Regardless of the level of sedation, supplemental oxygen is regularly administered to all patients to prevent hypoxia. Conventionally, it is delivered via nasal prongs and/or an extension tubing attached to the mouth guard (the application of the endoscope in the oral cavity precludes the use of normal face masks). The recommended flow rate through the low flow nasal cannula is 2–4 L/min, while the inspired FIO_2_ (fractional inspired oxygen concentration) is dependent on the ventilatory minute volume, in the range of 0.27–0.50 [12, 13]. Patients with high American Society of Anesthesiologists (ASA) status (III) [5, 14], high body mass index (BMI) [5, 15] and those with obstructive sleep apnoea (OSA) [16] are especially at an increased risk of hypoxia during advanced endoscopic procedures such as ERCP; these patients will obtain most benefit from any improvement in oxygenation techniques. It has been the case that superior oxygen delivery options preserving spontaneous respiration without interfering with the pharyngeal cavity have been limited for these procedures.

High-flow nasal cannula (HFNC) is a new approach for improving oxygenation and ventilation that has gained popularity in procedural sedation. It has been demonstrated to provide better oxygenation compared to the venturi face mask and low-flow nasal cannula during intravenous sedation for both bronchoscopy and dental procedures [17, 18]. HFNC can provide a maximum flow up to 70 L/min and delivers a flow-dependent positive airway pressure which increases end-expiratory lung volume and thereby improves oxygenation [19]. It has numerous physiological advantages that are not possible through standard (ventilation dependent) low-flow delivery systems. These advantages include the ability to create PEEP (up to 5–7.5 cm H_2_0), reduce the work of breathing, provide constant FIO_2_ up to 100%, provide good humidification, and aid washout of the pharyngeal dead space [19, 20]. In one centre, introducing the option to use HFNC affected anaesthetic practice and decreased the usage of general anaesthesia with an endotracheal tube (for a mixed group of ERCP and endobronchial ultrasound procedures) [21]. This observational study also showed HFNC also decreased the anaesthesia only time.

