### Intervention and comparison

Patients will be randomly allocated (computer-generated randomisation) to either the low-flow nasal oxygen group (group L; n = 66) or the high-flow nasal oxygen group (group H; n = 66). In group L, the procedure will be performed under deep sedation and analgesia, with supplemental oxygen 4 L/min via regular nasal cannula and a further supplemental oxygen source with a flow rate of 4 L/min administered through an extension tubing attached to the mouth guard. In group H, the procedure will be performed under deep sedation and analgesia similar to Group L, with oxygen delivered through a HFNC. This will be accomplished using the Optiflow THRIVE (Transnasal Humidified Rapid Insufflation Ventilatory Exchange) device (Opti-Flow, Auckland, New Zealand). Flow rate through the cannula will be commenced at 30 L/min and fractional inspired oxygen concentration will be set at 100%. The flow will be gradually increased after the administration of sedative agents and will be maintained at 50 L/min during the procedure. The flow rate may be either increased up to 70 L/min if necessary or decreased to 30 L/min if the patient does not tolerate the higher flow rate (50 L/min is very well tolerated in even very lightly sedated patients).

Standard monitoring will be applied, including continuous electrocardiogram, blood pressure automatically measured every 3 min, transcutaneous capnography and pulse oximetry. The procedures will be done in either the lateral or prone positions. A standard sedation technique will be applied for both groups. Sedation is to be provided by titrated doses of fentanyl 0.5–1.0 mcg/kg, as required, and a propofol target controlled infusion (using the Marsh model) commencing at an initial plasma target of 1.5–2.0 mcg/mL and titrated up or down during the procedure, between target values of 1–4 mcg/mL based on satisfactory depth of anaesthesia and frequency of ventilation (8–14 breaths per min). Administration of further fentanyl top up doses (25 mcg) will be at the anaesthetist’s discretion. In all cases, airway obstruction needs to be avoided.

If it is deemed necessary that during the intervention phase, if the participants’ clinical condition warrants an advanced airway such as tracheal intubation, it will be undertaken and they will be retained in an intention-to treat analysis.

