#### Secondary outcomes

Secondary outcomes are as follows:
Number of events of hypoxia, defined as desaturation < 90%. The mean number of events during the procedure will be compared between the two groups;Lowest recorded SpO_2_ during the procedure;Transcutaneous CO_2_. Maximum value recorded and average value during the case. The mean values during the procedure will be compared between the two groups;Lowest recorded SpO_2_% during the procedure. The mean values during the procedure will be compared between the two groups;Requirement of minor airway manoeuvres: jaw lift/jaw thrust, nasopharyngeal airway insertion. Proportion of patients requiring these manoeuvres will be compared between the two groups;Requirement of major airway manoeuvres: bag mask ventilation, endotracheal intubation. Proportion of patients requiring these manoeuvres will be compared between the two groups;Arrhythmia (any change in cardiac rhythm observed on the electrocardiogram). Proportion of patients manifesting arrhythmia during the procedure will be compared between the two groups;Total fentanyl dose. The mean values (the doses in micrograms) during the procedure will be compared between the two groups;Requirement of antispasmodic agent. Proportion of patients requiring this medication will be compared between the two groups;Total duration of procedure (starting from sedation until leaving the suite). The mean duration in minutes will be compared between the two groups;Duration under sedation/anaesthesia: measured from the time of induction till eye opening. The mean duration in minutes will be compared between the two groups;Successful completion of the procedure: Yes/No. Proportion of patients fulfilling this criterion will be compared between the two groups;Early complications – elicited as patients leave recovery;Dry mouth/nose/throat: binary outcome (constant pain or discomfort in the mouth/nose/throat). Proportion of patients experiencing this adverse event will be compared between two groups:
◦ Sensation of abdominal bloating: Y/N. Proportion of patients experiencing this adverse event will be compared between the two groups;Patients’ satisfaction score on leaving recovery: 5 points numerical rating scale:

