## Discussion

The increasing demand for ERCPs on a cohort of patients with multiple co-morbidities, along with time constraints in optimising these patients when it is attempted on a semi-urgent basis, has generated an enormous interest in the quest for exploring better airway management strategies. HFNC is one such device that has been attempted across a variety of settings requiring sedation. Besides the primary outcome assessing the occurrence of hypoxia, secondary outcomes of airway intervention and patient-reported scales are also measured.

The risks are very negligible from these two nasal cannulas. They have been in use for many years as standard methods of delivering oxygen. The patients will be asked for symptoms of dryness of mouth or throat or nose after the procedure as part of outcome measures. If dryness develops, it normally settles within a few hours. These outcome measures are aimed at detecting some of the known side effects of oxygen delivery. The HFNC can cause abdominal distension, particularly in children after prolonged use. At the end of this procedure, endoscopists routinely evacuate any insufflated gas from the stomach and this will mitigate any such risk in this group. There are no other specific safety issues concerning HFNC for participants and administering staff.

The results may lead to improved outcomes and reduce airway-related complications in patients undergoing ERCPs. In our opinion, the results will also deliver meaningful information on the role of HFNC-assisted sedation in any setting.

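### The dryness outcome is scored on constant pain or discomfort, which conflicts with its label and with the Discussion and makes the between-arm comparison of dryness non-specific and probably diluted

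*Protocol article*

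**What the plan says.** The Secondary outcomes section of the Protocol article labels the item as dryness of the mouth, nose or throat and gives the scoring rule directly after the label: "binary outcome (constant pain or discomfort in the mouth/nose/throat". The item sits under the entry "Early complications – elicited as patients leave recovery", and its analysis is stated as "Proportion of patients experiencing this adverse event will be compared between two groups". The only other symptom asked of patients there is abdominal bloating.

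The Discussion returns to the same item: "The patients will be asked for symptoms of dryness of mouth or throat or nose after the procedure as part of outcome measures". It gives the purpose as follows: "These outcome measures are aimed at detecting some of the known side effects of oxygen delivery". It does not mention pain, discomfort or constancy.

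Two further statements bear on which arm might be drier. The Background lists among the advantages of HFNC that it can "provide good humidification, and aid washout of the pharyngeal dead space". The low-flow arm is treated "with supplemental oxygen 4 L/min via regular nasal cannula and a further supplemental oxygen source with a flow rate of 4 L/min", the second source being attached to the mouth guard. No humidification is stated for that arm.

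**The concern.** The scoring rule does not contain the symptom that the outcome is named for. Dryness and constant local pain or discomfort overlap, but neither implies the other. All patients have an endoscope passed through the mouth and throat, and some may need a nasopharyngeal airway or a tracheal tube. Soreness can therefore arise whatever the oxygen method, and the rule has nothing that excludes it.

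At stake is the meaning of one of two patient-elicited symptoms in a trial whose stated aim covers safety as well as efficacy. A result of no difference could mean that the arms are equally dry, or only that the item did not measure dryness. If the recovery form asks only the pain question, no later analysis can recover the dryness data.

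**Working it through.** **Step 1: the two descriptions side by side.**

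| Patient on leaving recovery | Secondary outcomes rule | Discussion description |
|---|---|---|
| Dry, constantly uncomfortable or painful | yes | yes |
| Dry, but not painful and not constantly uncomfortable | no | yes |
| Not dry, constant soreness (for example from instrumentation) | yes | no |
| Not dry, not sore | no | no |

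The second and third rows disagree, so the two sections cannot both govern the form. Because the rule includes discomfort as well as pain, dryness that is painless but constantly uncomfortable is still counted.

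**Step 2: the effect on the comparison.** The article states no rate, power or sample size for dryness, so there is no figure of its own to reproduce. Let p be the true proportion with dryness in an arm, s the share of dry patients who meet the rule because of their dryness, and b the share of patients with constant soreness from other causes. With s and b equal in both arms and soreness independent of dryness:

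- observed rate = 1 − (1 − s·p)(1 − b)
- observed difference = s·(1 − b) × true difference

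The multiplier s(1 − b) cannot exceed 1, so the difference shrinks whichever arm is drier.

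**Step 3: illustration.** The 66 per arm comes from the Sample size calculation section. All rates, s and b are assumptions. Power is for a two-sided 5% test of two proportions by the normal approximation, with pooled variance under the null. The article gives alpha 0.05 without sidedness.

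For true rates of 20% and 40%, s = 0.5 and b = 0.2:

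- drier arm: 1 − (1 − 0.5 × 0.40)(1 − 0.2) = 1 − 0.80 × 0.80 = 0.36
- other arm: 1 − (1 − 0.5 × 0.20)(1 − 0.2) = 1 − 0.90 × 0.80 = 0.28
- difference: 0.5 × 0.8 × 20 = 8 percentage points

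| Assumed true rates | Dryness itself recorded (s = 1, b = 0) | Threshold only (s = 0.5, b = 0) | Other soreness only (s = 1, b = 0.2) | Both (s = 0.5, b = 0.2) |
|---|---|---|---|---|
| 10% v 30% | 83% | 48% (5% v 15%) | 48% (28% v 44%) | 17% (24% v 32%) |
| 20% v 40% | 71% | 36% (10% v 20%) | 46% (36% v 52%) | 16% (28% v 36%) |
| 30% v 50% | 65% | 30% (15% v 25%) | 45% (44% v 60%) | 16% (32% v 40%) |

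Cells give power, with the observed rates in brackets.

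**Step 4: how firm the direction of bias is.** Shrinkage towards no difference needs s and b to be alike in the two arms. That is plausible for the endoscope, which both arms share, but it is not guaranteed. The trial expects fewer respiratory events with HFNC, so airway manoeuvres, and soreness from them, could differ by arm. Patients and investigators are also unblinded. Dilution is therefore probable, not certain.

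**The case against.** The strongest reply is that the parenthesis is a severity threshold: the patient is asked about dryness, as the Discussion says, and is scored yes only if it causes constant pain or discomfort. On that reading soreness without dryness is not counted, b is zero, and what is lost is the mildest part of a symptom that the Discussion says normally settles within hours. The form is not shown, and an article condenses the full protocol. This reading is possible, but it is not what the sentence says: the rule nowhere requires dryness. Even if it were accepted, the Discussion sets no such threshold, and the threshold-only column above would still apply.

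It is also fair to say that the trial is powered for hypoxia, not for dryness; that every rate in the illustration is assumed; and that other harms are recorded, including arrhythmia, airway manoeuvres, transcutaneous carbon dioxide, bloating and serious adverse events. These points stand, and they limit the weight of the finding.

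A reader might infer more than the documents allow, in three ways:

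- **That all painless dryness is missed.** It is not, because discomfort also qualifies.
- **That the rule masks a known harm of HFNC.** The Discussion attributes dryness to oxygen delivery by both cannulas, and the Background counts good humidification in favour of HFNC. The low-flow arm could be the drier one. The effect that the Discussion ties to HFNC is abdominal distension, which is covered separately by the bloating item.
- **That the negligible-risk statement in the Discussion rests on this item.** It rests on years of prior use of both cannulas.

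**Conclusion.** The contradiction is real and can be seen in the text: label, scoring rule and Discussion do not describe the same symptom. Scored as written, the item is a non-specific measure of dryness, and a between-arm difference in dryness would probably be pulled towards zero. The direction of any hidden difference is unknown, so a harm or a benefit of HFNC could be obscured.

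The size cannot be fixed from the article. Over the assumed settings shown, power falls from 65–83% with dryness itself recorded to 30–48% with one mechanism acting and 16–17% with both. These figures depend on the assumed rates, on s and b being equal in the two arms, and on a two-sided test. The point concerns one secondary tolerability outcome and has no bearing on the primary outcome or the sample size.

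**What to change.** Reconcile the Secondary outcomes and Discussion sections. Define the outcome as dryness of mouth, nose or throat on leaving recovery, yes/no, and record local pain or discomfort as a separate yes/no item. Use identical question wording in both arms, since neither patients nor investigators are blinded.

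The cost is one reworded and one added question on a form completed once in recovery, a change to the outcome list, and an amendment notified to the three sites. Recruitment began in February 2019 and the article reports the trial on hold, so some patients may already have answered the old question. They should be reported according to the question they were actually asked. If the form has asked only about pain or discomfort, the dryness comparison will then rest on fewer than 66 per arm. If the form has asked about dryness all along, correcting the definition in the outcome list is enough to repair the dryness outcome.

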### Sample size calculation

A 21.4% incidence of hypoxia (SPO_2_ < 90% for 15 s) was noted in an Australian study during ERCP with propofol sedation in older patients (20). Assuming a 16% reduction in hypoxic events by employing the HFNC technique (given the rate of hypoxia as 21.4% in the sedation group and an estimated 5.4% in the HFNC group), with a power of 80% and an alpha error of 0.05, a total of 132 patients would be required (66 in each arm).

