## Background

Endoscopic retrograde cholangiopancreatography (ERCP) is a common intervention in the treatment of biliary and pancreatic diseases, and the demand for ERCP is increasing. There are several difficulties for the anaesthetist to deal with. It is generally performed in a prone or lateral position under moderate to deep sedation or general anaesthesia [1–3]. In most hospitals, ERCP is usually performed outside the operating room. The patients who require this procedure are typically elderly with significant co-morbidities. General anaesthesia with an endotracheal tube may be a ‘safe option’ in the prone position in terms of having a secured airway and a lower ERCP failure rate [3]; there may be a reduction in complication rates, but intubation has drawbacks. In addition to the well-known problems associated with insertion of the tube, managing a paralysed intubated patient prone creates its own challenges. Note that there is frequently a prolongation of anaesthetic time concurrent with the use of muscle relaxants.

Deep sedation using propofol is perhaps the most commonly employed technique for ERCPs. ERCP generally requires a deeper level of sedation compared to simple gastroscopy and there is an increased risk of both partial and complete airway obstruction. The goals of deep sedation are: preserving adequate spontaneous ventilation; maintaining cardio-respiratory stability; early recovery; and minimising any hypoxaemia at all times. Hypoxemia and aspiration have occurred when these procedures have been performed under deep sedation, especially in high-risk cases [4]. Reasons for desaturation during ERCP under deep sedation have been attributed to reduced cardiopulmonary reserve, advanced age, respiratory depression, duration of the procedure, and prone positioning. The incidence of hypoxemia during any endoscopic procedure is in the range of 11%–50% [5–7] and it is possibly as high as 60% with ERCP [8] (definitions of hypoxia vary between the studies). Prolonged hypoxia is a major risk factor for periprocedural cardiac arrhythmias and myocardial ischaemia [9–11]. Any methods of avoiding such occurrences is worthy of investigation.

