### Outcome measures

#### Primary outcome

The occurrence of hypoxia, defined by any event of SpO2 (oxygen saturation measured by pulse oximetry) < 90% of any duration, will be compared between the two groups.

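### The 80% power for 132 patients is calculated from a 15-second hypoxia rate, but the primary outcome counts desaturation of any duration, so the stated power is not that of the endpoint tested

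*Protocol article*

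**What the plan says.** In the protocol article, the section Sample size calculation opens with the planning rate and its definition: "A 21.4% incidence of hypoxia (SPO_2_ < 90% for 15 s) was noted in an Australian study during ERCP". It then fixes the effect, "given the rate of hypoxia as 21.4% in the sedation group and an estimated 5.4% in the HFNC group", and concludes "with a power of 80% and an alpha error of 0.05, a total of 132 patients would be required (66 in each arm".

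The section Primary outcome defines the event as SpO2 "< 90% of any duration, will be compared between the two groups". The Abstract likewise counts any event below 90%.

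The Background shows that the authors know definitions matter. It gives 11% to 50% for endoscopic procedures in general, and for ERCP says "it is possibly as high as 60% with ERCP [8] (definitions of hypoxia vary between the studies").

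No section converts the 21.4% or the 5.4% from the 15-second definition to the any-duration definition.

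**The concern.** The planning event and the tested event are different. Every desaturation that lasts 15 s is also a desaturation of any duration, but the reverse is not true. In one and the same population the any-duration rate is therefore at least as high as the 15-second rate, and it is higher wherever some patients have only brief dips.

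Dropping the duration requirement can change both arms' rates and the difference between them. If brief dips occur about as often with either cannula, they add events to both arms and narrow the contrast. If HFNC prevents brief dips as effectively as sustained ones, the contrast widens. The article does not say which it expects.

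The sample size section is the only justification given for 132 patients. A result that is not significant would be read as coming from a trial with 80% power, when no power has been worked out for its own primary endpoint.

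**Working it through.** **Inputs from the protocol article.** Control rate 21.4% and HFNC rate 5.4%, on the 15-second definition; alpha 0.05; power 80%; 66 per arm (Sample size calculation). Allocation 1:1 (Randomisation). Endpoint of any duration (Primary outcome). Sidedness is not stated; two-sided is assumed.

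**Method.** Exact power of the uncorrected chi-square test: sum the product of the two binomial probabilities (n = 66 each) over all pairs of event counts (x, y) for which |x − y|/66 ÷ √[p̄(1 − p̄) × 2/66] exceeds 1.96, where p̄ = (x + y)/132.

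**Step 1: reproduce the plan's figure.** 21.4% vs 5.4% gives 79.97%, which matches the stated 80%. The arcsine formula gives a total of 130, also close. (The pooled normal formula gives 140, and Fisher's exact test at 66 per arm has 72.4% power, so the match depends on the test chosen.)

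**Step 2: the size of the planned effect.** Absolute: 21.4 − 5.4 = 16.0 percentage points. Relative: 16.0/21.4 = 74.8%, a relative risk of 0.25.

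**Step 3: power for the any-duration endpoint.** The article gives no any-duration rate for this cohort, so the control rates below are assumptions. They run from the planning rate's neighbourhood up to the 60% quoted in the Background.

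| Assumed control rate | 16-point difference kept | Risk halved |
|---|---|---|
| 25% | 70% (vs 9%) | – |
| 30% | 61% (vs 14%) | 55% (vs 15%) |
| 40% | 51% (vs 24%) | 72% (vs 20%) |
| 50% | 45% (vs 34%) | 86% (vs 25%) |
| 60% | 44% (vs 44%) | 94% (vs 30%) |

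With the full relative reduction kept, a 30% control rate gives 30% × 0.252 = 7.6% on HFNC and 93% power.

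**Step 4: brief dips equally common in both arms.** Let a share b of patients without a 15-second event have a briefer dip, with the same b in each arm. Each rate then becomes p + (1 − p)b.

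- b = 5%: 0.214 + 0.786 × 0.05 = 25.3% vs 0.054 + 0.946 × 0.05 = 10.1%; power 64%.
- b = 10%: 29.3% vs 14.9%; power 52%.
- b = 20%: 37.1% vs 24.3%; power 36%.

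Across these scenarios power at 66 per arm runs from 36% to 94%.

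**The case against.** The strongest reply is that nothing here shows the trial to be too small. A reader might infer that it is underpowered, and the documents do not support that. At higher control rates an effect well short of the planned 75% reduction is enough: 40% vs 18%, a 55% reduction, gives 81%, and halving gives 86% at 50% and 94% at 60%. This stands, and the point is limited accordingly.

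A reader might also infer that the cohort's risk profile pushes the rate up further. The planning rate comes from ERCP "during ERCP with propofol sedation in older patients (20"), while this trial enrols adults with ASA 3 or 4, obesity or sleep apnoea. But the Background describes ERCP patients as typically elderly and comorbid, so the groups may overlap. The exclusion criteria remove some of the highest-risk patients, and group L receives "a further supplemental oxygen source with a flow rate of 4 L/min administered through an extension tubing attached to the mouth guard". The direction of any population effect is not established, and nothing here rests on it.

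Nor is this an arithmetic error, since 132 follows from its inputs. The phrase "Assuming a 16% reduction in hypoxic events by employing the HFNC technique" is loose wording only, because both rates follow in the same sentence.

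Finally, the mismatch does not bias the estimate or affect type I error, and the Statistical analysis section plans 95% confidence intervals, which would show the imprecision of a null result. That is true and limits the harm. It does not make the quoted 80% correct. Nor can condensation into an article explain the problem: both definitions are printed, and they differ.

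**Conclusion.** The point holds as a mismatch in a planning input. The 80% is the power to detect 21.4% vs 5.4% on a 15-second definition, while the trial tests an any-duration definition for which no rates or power are given. The one firm directional statement is that, in a given population, the any-duration rate cannot be below the 15-second rate. Whether power is higher or lower than 80% is unknown.

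The size of the uncertainty is large. Power falls to between 44% and 70% if the 16-point difference is kept at control rates of 25% to 60%, and to between 36% and 64% if brief dips are added equally to both arms. It runs from 55% to 94% if risk is halved at control rates of 30% to 60%, and is 93% at 30% if the full relative reduction holds. These figures assume a two-sided uncorrected chi-square test, 66 analysed per arm, and control rates that are illustrative and not taken from data on this cohort.

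**What to change.** Keep 132 patients and keep the primary endpoint. In the sample size section:

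- State that 21.4% and 5.4% refer to SpO2 below 90% lasting 15 s.
- Replace the single 80% with a short power table for the any-duration endpoint at 66 per arm, over control rates from 21.4% to 60%, showing effects on both the absolute and the relative scale. Name the test and its sidedness.
- Describe the planned effect as 16 percentage points (75% relative).

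Add SpO2 below 90% for at least 15 s as a supporting analysis, run in the same way as the primary, if event duration is recorded or can be retrieved. Record duration prospectively for the remaining patients. The outcome sections list occurrence, number of events and lowest SpO2, but no duration, and recruitment began in February 2019. Durations may therefore be missing for patients already enrolled, and the report should say for how many.

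The cost is one paragraph, one table, one added data field and one added analysis. The downside is a stated power that is less favourable or less certain. The Trial status section reports the trial as on hold, so an amendment is practical now.
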